## Model development and validation

Quality control will be applied throughout model development and evaluation. Model complexity will be controlled through prespecification of predictors and the use of penalised regression to reduce overfitting and ensure consistency with the available sample size. Internal validation will be performed using bootstrap resampling to assess optimism in model performance. Evidence of substantial optimism or unstable performance will be taken as an indication of overfitting and will lead to model simplification or stronger penalisation. Model performance will be judged based on both discrimination and calibration. Poor calibration or inconsistent performance across resamples will be transparently reported. Decision-curve analysis will be used as an additional check of potential clinical usefulness**.**

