## Statistical methods and analysis

The data will be analysed using R Studio. The normality of the distribution will be verified via the “Kolmogorov‒Smirnov test”. If the data are normally distributed, they will be presented as the mean ± SD; if they are not normally distributed, they will be presented as the median and interquartile range. Categorical variables will be presented as frequencies and percentages, or as medians and interquartile ranges. Spearman/Pearson correlation coefficients will be applied to all predictors and outcomes. Candidate predictors will be specified by using Penalised regression methods (elastic net) for model development to achieve coefficient shrinkage and reduce overfitting.

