## Internal validation and model performance

Internal validation will be performed using bootstrap resampling to obtain optimism-corrected estimates of model performance. Model calibration will be evaluated by reporting the calibration intercept and calibration slope. Discrimination of the model will be assessed using the area under the receiver operating characteristic curve (AUC). Overall model performance will be quantified using the Brier score. The primary endpoint will be analysed as a (ΔFMA) as continuous outcome. Secondary analyses will explore clinically meaningful dichotomous thresholds for recovery based on published guidelines and expert consensus. Decision-curve analysis will be used to assess the net clinical benefit of the prediction model across a range of clinically relevant thresholds. In addition, repeated cross-validation using leave-one-out cross-validation (LOOCV) will be conducted as a sensitivity analysis to evaluate the robustness of model performance estimates.

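### Leave-one-out AUC and calibration slope run low for an elastic-net model, so the planned robustness check will tend to disagree with the bootstrap even when the model is sound (minor)

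*Protocol article*

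**What the plan says.** The protocol article's section Statistical methods and analysis chooses "Penalised regression methods (elastic net) for model development to achieve coefficient shrinkage and reduce overfitting".

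The section Internal validation and model performance sets the main validation: "Internal validation will be performed using bootstrap resampling to obtain optimism-corrected estimates of model performance". It lists the measures as AUC, Brier score and calibration: "Model calibration will be evaluated by reporting the calibration intercept and calibration slope". The primary endpoint there is the change in FMA as a continuous outcome; dichotomies are secondary. The section closes with repeated cross-validation in leave-one-out form: "leave-one-out cross-validation (LOOCV) will be conducted as a sensitivity analysis to evaluate the robustness of model performance estimates". It does not say which measures leave-one-out will report, how they will be scored, or how close to the bootstrap they should be.

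The section Model development and validation states the response to poor results: "Evidence of substantial optimism or unstable performance will be taken as an indication of overfitting and will lead to model simplification or stronger penalisation". That sentence follows one on the bootstrap and does not mention leave-one-out.

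**The concern.** A sensitivity analysis is useful only if, for a sound model, it is expected to agree with the main analysis. Leave-one-out scoring of AUC and slope lacks that property for a shrunken model. When a patient with a high outcome is removed, the mean of the remaining patients falls, and so does the prediction for that patient. The more the model shrinks towards the mean, the more this matters.

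The plan would then set an approximately unbiased bootstrap AUC beside a leave-one-out AUC that is low by construction. A reader of the results could take the gap as a sign of overfitting. Heavier penalisation in response would widen the gap.

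**Working it through.** **1. The plan's own sample size.** Sample size estimation uses n = Z²(1 − r²)/d² with Z = 1.96, r = 0.6, d = 0.20: 3.8416 × 0.64 / 0.04 = 61.5, stated as 61. With 20% dropout, 61/0.8 = 76.25, stated as 76. Both reproduce. The checks below use n = 61.

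**2. Mechanism.** If the elastic net keeps no predictor, the prediction for left-out patient i is pᵢ = (S − yᵢ)/(n − 1), where S is the sum of all outcomes. Rearranged, yᵢ = S − (n − 1)pᵢ. Prediction and outcome therefore correlate at exactly −1, the linear calibration slope is −(n − 1) = −60, and for a binary outcome the AUC is 0 instead of 0.5. This is a limiting case; a model with real predictors is affected only in part, so its size has to be simulated.

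**3. Simulation inputs.** From Sample size estimation: n = 61, about 7 predictor parameters, anticipated AUC 0.75–0.80, and r = 0.6, which gives R² = 0.36 if r is read as the model's multiple correlation. Assumed, because the article gives no value: 40% events, predictor correlation 0.5, elastic-net mixing 0.5, and penalty fixed at 0.03, 0.1 or 0.2 or tuned by inner 5-fold cross-validation. Truth is the same fitted model's performance in 20,000 new patients. There were 180 datasets per fixed-penalty setting and 60 per tuned setting.

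**4. Binary outcome** (mean AUC; median slope):

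| Penalty | True AUC | Leave-one-out AUC | Gap | Bootstrap AUC | True slope | Leave-one-out slope |
|---|---|---|---|---|---|---|
| 0.03 | 0.769 | 0.733 | 0.036 | 0.770 | 0.87 | 0.70 |
| 0.1 | 0.774 | 0.731 | 0.043 | 0.780 | 1.33 | 1.10 |
| 0.2 | 0.768 | 0.701 | 0.067 | 0.779 | 2.27 | 1.71 |
| tuned | 0.765 | 0.690 | 0.075 | 0.766 | 1.23 | 0.85 |
| 0.03 | 0.718 | 0.680 | 0.038 | 0.724 | 0.78 | 0.64 |
| 0.1 | 0.727 | 0.677 | 0.050 | 0.732 | 1.29 | 0.96 |
| 0.2 | 0.720 | 0.621 | 0.099 | 0.734 | 2.29 | 1.38 |
| tuned | 0.710 | 0.599 | 0.111 | 0.719 | 1.15 | 0.72 |

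Across these settings leave-one-out fell more than 0.10 below the truth in 18–41% of datasets, and the bootstrap in 3–8%. The Monte Carlo standard error of the gap at true AUC about 0.77 is 0.006–0.008 for fixed penalties and about 0.02 for the tuned one.

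Range over the assumptions, at the weaker signal: with 20% events the gap is 0.727 − 0.633 = 0.094 (penalty 0.1) and 0.698 − 0.562 = 0.136 (tuned). With n = 76, tuned, it is 0.721 − 0.681 = 0.040.

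**5. Continuous outcome** (ridge linear model, 400 datasets, three penalties, median slope):

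| R² | True slope | Leave-one-out slope | Shift |
|---|---|---|---|
| 0.36 | 0.87 / 1.06 / 1.47 | 0.81 / 1.00 / 1.37 | 0.06 / 0.06 / 0.10 |
| 0.15 | 0.64 / 0.91 / 1.44 | 0.52 / 0.77 / 1.07 | 0.12 / 0.14 / 0.37 |

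A separate simulation with a tuned elastic net and nine predictors gave 0.97 against 0.70 at R² 0.15. In the same simulation, leave-one-out R² from squared error showed no downward bias (0.287 true, 0.296 leave-one-out, at R² 0.36).

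**6. Does another scheme avoid it?** In 150 further datasets at penalties 0.03/0.1/0.2, true AUC was 0.769/0.774/0.769 and leave-one-out AUC 0.741/0.740/0.713. Repeated stratified 5-fold cross-validation, with AUC computed within each held-out fold, gave 0.763/0.772/0.766. Estimates more than 0.10 too low occurred in 15–26% of datasets for leave-one-out and 5–7% for stratified 5-fold. In the nine-predictor simulation with tuning, at R² 0.36, the figures were 0.74 true, 0.69 leave-one-out and 0.73 within-fold 5-fold.

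**7. Slopes within small folds.** Ten folds of 61 hold about 6 patients each. With 2 events, 4 non-events and AUC 0.74, about 27% of folds are completely separated, which makes the logistic slope infinite. The chance of at least one such fold in a pass is 1 − 0.73¹⁰ = 0.96. For 5-fold (5 events, 7 non-events) it is about 16% per pass. An average of within-fold slopes is therefore not usable.

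**The case against.** The best defence is that nothing in the plan depends on this result. The bootstrap is the main validation and is accurate in the planned range. Leave-one-out is a sensitivity analysis without a threshold, and which measures it reports may be settled in a fuller document. All of this stands, and it limits the severity. It does not remove the point: the article names leave-one-out as the check of performance estimates that include AUC and slope, and neither can be scored from one patient without pooling.

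A reader might go further and infer that a low leave-one-out result would oblige the team to penalise more heavily, until a usable model is emptied and sEMG is wrongly declared uninformative. The documents do not support that. The rule in Model development and validation follows the bootstrap sentence, does not mention leave-one-out and sets no margin. Misreading is a risk, not a written rule.

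Three further limits stand. AUC concerns only the secondary dichotomies; for the continuous primary endpoint the slope shift at R² 0.36 is small. A lower slope is not always a worse one: where the true slope exceeds 1, leave-one-out may land nearer 1 (1.06 against 1.00). The extreme values, such as an AUC of 0 or a slope of −60, belong to empty models.

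It can also be said that a gap of 0.05 is smaller than the standard error of an AUC at this size (about 0.068 by Hanley–McNeil with 40% events). But the bootstrap and leave-one-out use the same patients and share much of that error, so a systematic difference between them is still misleading.

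**Conclusion.** The point holds as a minor one. For the planned elastic net, pooled leave-one-out AUC and calibration slope are biased downward. With 61 patients and a true AUC of about 0.75–0.77 the AUC shortfall is about 0.03–0.08. It grows with weaker signal, heavier penalty or fewer events. For the continuous FMA outcome the slope shift is about 0.06–0.10 at R² 0.36 and 0.12–0.37 at R² 0.15.

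The direction follows from the algebra. The size rests on assumed event rate, predictor correlation, mixing and penalty, and on ridge models for most of the continuous results. The consequence is that a gap between leave-one-out and the bootstrap is expected for a sound model and is not evidence of instability. The bootstrap results and the primary endpoint analysis are not put in doubt.

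**What to change.** In Internal validation and model performance:

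- Replace the leave-one-out check with repeated stratified 5-fold cross-validation, with the penalty tuned inside each training fold. This also removes a wording fault: leave-one-out has only one partition, so it cannot be repeated.
- For dichotomised outcomes, compute AUC within each held-out fold and average over folds and repeats.
- Do not average within-fold calibration slopes. Take the slope from the optimism-corrected bootstrap, or fit it once per repeat on predictions pooled over the stratified folds. The pooled option was not simulated here.
- Keep leave-one-out, if wanted, for squared-error measures only: RMSE or R² for continuous FMA, Brier score for dichotomies.

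In Model development and validation, state that a pooled leave-one-out AUC or slope does not count as evidence of instability.

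The cost is a few lines of wording and a little computing time. Fold-level estimates are slightly noisier, which repetition reduces. No new patients or data are needed.

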## External validation

Following internal validation, external validation in an independent or temporally distinct cohort will be conducted in future work to further evaluate model generalizability and clinical utility.

## sEMG analysis

Sensitivity analyses will be conducted where feasible to assess the robustness of the primary association between early sEMG amplitude reflecting voluntary muscle activity in the absence of visible movement and subsequent motor recovery. These secondary analyses will evaluate whether reasonable variations materially influence model performance in signal-processing assumptions and will be reported as supplementary without modifying the predefined primary analytical approach. Exploratory analysis will examine the association between early sEMG amplitude and SAFE scores recorded at baseline to provide preliminary evidence of convergent validity. Spearman correlation coefficients (ρ) with 95% confidence intervals will be reported

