## Abstract

Stroke is a leading cause of long-term disability, resulting in motor impairments that significantly affect the quality of life. Predicting motor recovery is particularly difficult for people with severe motor impairment early after stroke. Traditional assessments are limited in terms of residual muscle activity, which is crucial for tailoring rehabilitation interventions. Incorporating surface electromyography (sEMG) assessment can provide a deeper understanding of motor recovery potential in severe motor impairment. This prospective cohort study aims to develop a TRIPOD-compliant prediction model to examine whether sEMG amplitude recorded from five upper and four lower extremity muscles within the first week of stroke could predict motor recovery at 3 months post-stroke. This prospective study will include 76 participants between the ages of 18–80 years presenting first-ever anterior or middle cerebral artery stroke resulting in a severe motor impairment within the first week of stroke onset. In addition to sEMG recording to evaluate muscle activity, participants will undergo a comprehensive clinical assessment of motor functions and activity at the 1st and 3rd months following stroke onset. Multivariate regression analyses will be used to determine associations between sEMG metrics and recovery outcomes.

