## Specifications table

**Table utbl0001:** 

Subject area	Neuroscience
**More specific subject area**	Stroke
**Name of your protocol**	Predicting motor recovery using surface electromyography in people with severe motor impairment after stroke: A prospective cohort study protocol
**Reagents/tools**	• Electromyography (Delsys, Trigno wireless EMG 8-channel AD instrument, USA) • Action Research Arm Test Kit
**Experimental design**	Not applicable
**Trial registration**	CTRI/2025/06/088335
**Ethics**	Before the study commencement, all participants will provide written informed consent.
**Value of the Protocol**	• This study explores sEMG as an early biomarker of residual muscle activity, potentially enabling more accurate prediction of motor recovery in people with severe motor impairment than conventional clinical assessments alone. • By identifying patients with residual motor potential despite severe initial motor impairment, the resulting prediction model can guide individualized rehabilitation intensity and goal setting, optimizing functional outcomes. • Few studies have focused on individuals with severe motor deficits in the acute phase. This protocol generates novel evidence that could reshape prognostic practices and inform future research in this high-risk population.

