## Background

Stroke is a significant contributor to death and long-term disability worldwide [1]. Poststroke motor impairment is the most prevalent cause of adult disability, which has a major impact on healthcare worldwide [[2], [3], [4]]. Such impairments limit the capacity to carry out activities of daily living (ADL) [5], with >70% of stroke survivors experiencing hemiplegia affecting the upper or lower limbs, thereby affecting their functional independence [6]. According to International Classification of Functioning, Disability and Health (ICF) [7], motor functions encompass neuromusculoskeletal and movement-related functions, including muscle strength and endurance; voluntary movement control and coordination; and movement patterns related to walking, transfers, or upper body tasks [8].

Stroke recovery, in turn, refers to the extent to which functioning at different levels (body structure/function, activity capacity, and performance or participation) has returned to a prior stroke level [9]. Recovery is a multifaceted process that possibly combines spontaneous and learning-dependent processes, including restitution (repairing the impaired neural tissues), substitution (reorganizing partially impaired neural tissues to regain lost functions), and compensation (improving the gap between a patient's impaired skills and the demands of their environment) [10]. Even though recovery trajectories differ among individuals, several studies have suggested that recovery of body functions and activities is predictable even in the first days of stroke [10,11].

The capacity to estimate motor recovery would improve health resource use, individual-tailored rehabilitation programs, and patient and therapist expectations. Nevertheless, predicting motor function recovery remains a significant challenge owing to the high degree of variability among individuals, particularly when prediction relies solely on clinical evaluation [12]. While clinical assessment can serve as a strong independent predictor, particularly for patients with mild to moderate motor impairment [13], its predictive accuracy is more limited in those with severe deficits [13]. In such cases, adding neuroimaging and neurobiology biomarkers to prognostic models may help patients with severe motor impairments [[14], [15], [16]]. Unfortunately, the high expense, technical difficulty, and restricted accessibility of these methods in standard clinical practice limit their applicability [14].

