## Participants

We will include individuals aged 18–80 years, of any sex, with a first-ever ischemic or haemorrhagic stroke affecting the middle cerebral artery (MCA) or anterior cerebral artery (ACA). Recruitment will occur within seven days of stroke onset, and individuals reporting a Shoulder Abduction and Finger Extension (SAFE) score of <5(0–4) or knee extensor strength of <3/5 on the Medical Research Council (MRC) strength grade within this period will be included. Only those who are medically stable and able to follow simple commands will be included. The exclusion criteria will be individuals with a history of bilateral clinical strokes; those admitted more than seven days after stroke onset; patients who had undergone surgical interventions such as craniotomy or craniectomy; and individuals with pre-existing neurological or musculoskeletal disorders affecting motor functions.

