### Measurement time points

Independent variables (predictors) will be measured at two points: within 7 days of the first-ever stroke onset and at 1st month post-stroke. Dependent variables (outcomes) will also be assessed at two points, at the 1st and 3rd months post-stroke. (Table 1)

**Table 1 tbl0001:** Time points of predictor and Outcome measure assessment.

Measures		Within 7th day	1st Month	3rd Month
**Independent Variable** (Predictor)	sEMG recording of Upper limb muscles	**✔**	**✔**	
	sEMG recording of lower limb muscles	**✔**	**✔**	
**Dependent Variable** (Outcomes)	FMA-UE		**✔**	**✔**
	ARAT		**✔**	**✔**
	FMA-LE		**✔**	**✔**
	FAC		**✔**	**✔**
	10mWT		**✔**	**✔**
	Mini-BEST		**✔**	**✔**
	SIS		**✔**	**✔**

**Abbreviation:** FMA-UE, Fugl Meyer Assessment-Upper Extremity; ARAT, Action Research Arm Test; FMA-LE, Fugl Meyer Assessment-Lower Extremity; FAC, Functional Ambulation Category; 10mWT, 10-meter Walk Test; SIS, Stroke Impact Scale.

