## Missing data

We will make every effort to ensure completeness of follow-up data at respective time points. In cases where data is missing, multiple imputation methods will be employed to facilitate comprehensive data analysis. Missing data in predictors and outcomes will be handled using multiple imputations by chained equations (MICE), under the assumption that data are missing at random. The imputation model will include all candidate predictors, outcome variables, and relevant auxiliary variables (such as age, baseline motor severity, stroke type, and time from stroke onset to assessment) to preserve observed associations. Twenty imputed datasets will be generated, and estimates will be pooled using Rubin’s rules.

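### The stated value is better prediction than clinical assessment alone, but no clinical reference model is planned, so the results cannot show whether sEMG adds to the bedside examination

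*Protocol article*

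**What the plan says.** All references are to the protocol article.

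- **Stated value and rationale.** The Specifications table (Value of the Protocol) describes sEMG as "potentially enabling more accurate prediction of motor recovery in people with severe motor impairment than conventional clinical assessments alone". The Background supports this by saying of clinical assessment that "its predictive accuracy is more limited in those with severe deficits", and presents sEMG as able to detect activity that a clinical examination misses.
- **Predictors.** The section on independent variables and Table 1 list sEMG of the upper and lower limb muscles and nothing else. The Abstract gives "sEMG amplitude recorded from five upper and four lower extremity muscles within the first week of stroke". Sample size estimation anticipates about 7 predictors without naming them.
- **Baseline clinical severity.** Under Participants, entry requires a "Shoulder Abduction and Finger Extension (SAFE) score of <5(0–4) or knee extensor strength of <3/5 on the Medical Research Council (MRC) strength grade". SAFE returns only under sEMG analysis: "Exploratory analysis will examine the association between early sEMG amplitude and SAFE scores recorded at baseline to provide preliminary evidence of convergent validity". Missing data lists, separately from the candidate predictors, "relevant auxiliary variables (such as age, baseline motor severity, stroke type, and time from stroke onset to assessment". Background variables are recorded to describe the sample.
- **Performance.** The sections on model development, internal validation and uncertainty assess one model by AUC, calibration, Brier score and decision curve. They name no clinical-only model, no clinical-plus-sEMG model and no difference between models.

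**The concern.** The stated value is comparative, but the planned output is not. A good R² or AUC from an sEMG model shows that sEMG predicts recovery. It does not show that sEMG predicts anything a therapist could not already read from SAFE or a strength grade.

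The eligibility rule makes this more than a formality. Because the arm and leg criteria are joined by an *or*, a participant can enter on the leg with a mildly affected arm, or the reverse. Each limb's sample may therefore span a wide range of severity, and sEMG could predict partly by tracking that range.

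The one planned analysis that uses SAFE does not settle the matter, because it does not involve the outcome. A high sEMG-SAFE correlation would be consistent with convergent validity and equally with redundancy.

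At stake is whether the study can support its own argument for using sEMG in addition to a simple clinical examination.

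**Working it through.** **Reproducing the plan's sample size.** Inputs from Sample size estimation: z = 1.96, r = 0.6, d = 0.20, dropout 20%.

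n = z²(1 − r²)/d² = 3.8416 × 0.64 / 0.04 = 61.47, stated as 61. Then 61/0.80 = 76.25, stated as 76. Apart from rounding down, the figures reproduce. They rest on the precision of one marginal correlation, not on any increment over clinical severity.

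**What a marginal r of 0.6 implies for added value.** sEMG alone gives R² = 0.6² = 0.36. With SAFE (s) and sEMG (e) as two predictors,

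R² = (r_s² + r_e² − 2 r_s r_e r_se)/(1 − r_se²), and added R² = R² − r_s².

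Here r_e = 0.6 is borrowed from the sample size section, which does not say which variables it links. The values of r_s (SAFE-outcome) and r_se (sEMG-SAFE) are assumptions with no source in the document.

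| r_s | r_se | R², both | Added by sEMG |
|---|---|---|---|
| 0.5 | 0.5 | (0.61 − 0.30)/0.75 = 0.413 | 0.163 |
| 0.5 | 0.8 | (0.61 − 0.48)/0.36 = 0.361 | 0.111 |
| 0.6 | 0.5 | (0.72 − 0.36)/0.75 = 0.480 | 0.120 |
| 0.6 | 0.8 | (0.72 − 0.576)/0.36 = 0.400 | 0.040 |

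A wider set of assumptions runs from 0.223 (r_s 0.5, r_se 0.3) to about 0.000 (r_s 0.7, r_se 0.85). The same sEMG-only result, R² = 0.36, fits every one of these.

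**What 61 completers can resolve.** F test of the increment with SAFE and a single sEMG score in the model, alpha 0.05, f² = added R²/(1 − R²), noncentrality 61 f²:

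- Added R² 0.120: f² = 0.120/0.520 = 0.231, noncentrality 14.1, power about 96%.
- Added R² 0.040: f² = 0.040/0.600 = 0.067, noncentrality 4.1, power about 51%.

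**Parameter budget.** All nine muscles plus two clinical terms: 61/11 = 5.5 completers per parameter. Five arm muscles plus age and SAFE: 61/7 = 8.7. One summary score plus age and a clinical score: 61/3 = 20.3.

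**The case against.** The strongest reply is that the study never undertakes to show superiority. The Specifications table says only that sEMG has this potential. The formal aim and hypothesis, at the end of the Background, concern prediction by week-1 sEMG and its positive association with outcome. That is correct, and it means the primary aim needs no change.

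A reader might also infer that SAFE and strength are excluded from the model. No sentence says so. The roughly 7 predictors are unnamed, and the auxiliary list is illustrative. The absence is inferred from Table 1 and from the separate listing of severity under Missing data. But even if SAFE were one of the 7, no comparison between models is planned, so the gap remains.

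Three further points stand:

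- Knee-extensor grade in every participant is not stated. Under an *or* criterion, a person eligible on SAFE might have none recorded.
- sEMG is normalised as mean RMS over maximum RMS. If that maximum is the participant's own, much of the between-person difference in amplitude may be removed, so a strong correlation with SAFE cannot be presumed.
- The SAFE correlation is labelled exploratory and is not offered as evidence of added value.

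None of these supplies the missing reference model.

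**Conclusion.** The concern holds in a limited form. The protocol motivates sEMG by comparison with clinical assessment, and the analysis it describes contains no such comparison. Performance of the sEMG model alone will not show added value. The illustration puts the added R² at 0.04 to 0.16, against 0.36 for sEMG alone. Because the SAFE correlations are assumed, this range shows that the planned output cannot distinguish a substantial gain from a small one. It does not estimate the gain.

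Two stronger readings are not supported. One is that added value is untestable: the comparison is unplanned, and baseline SAFE at least will be available to make it. The other is that the sEMG effect is confounded: this is a prognostic model, in which a predictor that overlaps with severity is still valid. The overlap matters only for a statement about what sEMG adds.

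**What to change.** Keep the stated primary aim. Add a key secondary analysis, prespecified for each limb:

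1. A clinical reference model: age plus baseline SAFE for the arm, and age plus baseline knee-extensor MRC grade for the leg. First confirm that both are recorded for every participant, whichever criterion admitted them.
2. The same model plus week-1 sEMG, reduced to one or a few summary scores defined in advance.
3. The optimism-corrected difference between the two in R² and RMSE, and in AUC and net benefit for dichotomised outcomes, each with a bootstrap confidence interval.

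If this is not wanted, withdraw the comparison with clinical assessment from the Specifications table.

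The cost is mainly analysis-plan text, plus the check that both baseline scores are complete. The clinical terms use part of the parameter budget. With about 61 completers a small increment will be imprecise (about 51% power for an added R² of 0.04 with a single sEMG score), so the result should be read from its interval, and a non-significant difference should not be taken as proof that sEMG adds nothing.
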